### Risks and benefits

We do not expect any risks for the participants, except the risks following transportation to and from the educational site. The intervention is of educational character, no drugs or medical devices will be used. During the course there will be a nurse and/or medical doctor present. In case of adverse advents, the investigators will act according to their professions’ current ethical and professional standards.

If the intervention proves effective, benefits such as lower severity of occupational hand eczema, less sick leave, and diminished risk of exclusion from the work force are expected in the experimental group. A general improvement in health-related quality of life is also expected.

### Ethical considerations

The intervention is of educational character. The intention is to improve knowledge, behaviour, and consequently disease severity and absence from work, by an educational programme. No drugs or risk-full testing are used in the trial.

Medical treatment of the patients hand eczema will not be a part of this trial, and there will be no difference in access to the medical treatment in the experimental and control group.

Furthermore, as there is no existing evidence on the effect of more expensive interventions in this patient group, it is considered good ethical conduct to perform the described trial with a control group who are offered ‘treatment as usual’.

The main results of the trial will be presented to the included participants in a newsletter, where there will be references to any data published in medical journals.

### Trial conduct

The PREVEX trial will be conducted in compliance with the trial protocol and the Helsinki Declaration in its latest form. The protocol has been submitted for review to the Regional Ethics Committee for the Capital Region (journal number: H-1-2012-053), who replied that the PREVEX trial is not a ‘biomedical trial’, as no medicinal interventions take place, and accordingly a formal review by the Ethics Committee is not necessary. The trial has been approved be the Danish Data Protection Agency (journal number BBH-2011-33), and it has been registered on www.clinicaltrial.gov (identifier: NCT01899287).

### Sample size estimation

Calculations were made using ‘PS: Power and Sample Size Calculation’ version 3.0.14 [35]. A sample size was calculated for each of the three co-primary outcomes and the largest of the three sample sizes was chosen as the target sample size. To adjust for multiple testing, we divided the risk of type I error, 5%, by three, and we thus used a risk type I error of 1.67% and a risk of type II error of 20% (80% power). This calculation is based on the assumption that Holm’s procedure [36] will be used to adjust alpha (5%) to ensure that the family wise type I error will not exceed 5%. Holm’s procedure works as follows: let p(1), p(2) and p(3) be the observed P values where p(1) < p(2) < p(3) and H(1), H(2) and H(3) are the corresponding hypotheses. The hypotheses are tested in that order. At the J’th step H(J) is rejected if P(J) < 0.05/(3 – J +1). Otherwise H(J) and all other untested hypotheses are accepted and the procedure stops. Since we cannot know in advance which of the three outcomes will be associated with the smallest P value, the largest of the three sample sizes is chosen to secure that the power will be at least 80%.

For the continuous variable ‘total sick days’, we used unpublished data from the Working Environment Cohort (Arbejdsmiljøkohorten) from the National Research Centre for the Working Environment (http://www.arbejdsmiljoforskning.dk) to estimate the sample size. In this cohort of 9,786 healthy individuals, the mean number of sick days in year 2010 was 6.74 (95% confidence interval (CI) 6.32 to 7.15). We expect a higher degree of sick days in the PREVEX population, and we estimate that the mean number of total sick days in the PREVEX trial will be higher, probably about 20 sick days per year.

From the data above, we calculated the standard deviation (SD) using this formula:

$$\begin{array}{c} \mathrm{SD}=\sqrt{N}\times \frac{95\%\mathrm{CI}\;\mathrm{upper}\;\mathrm{limit}-95\%\mathrm{CI}\;\mathrm{lower}\;\mathrm{limit}}{3.92}\\ ⇓\\ \mathrm{SD}=\sqrt{9,786}\times \frac{7.15-6.32}{3.92}\\ ⇕\\ \mathrm{SD}=21.0 \end{array}$$

To detect a difference in total sick days of 5 days (25% risk reduction), we need 742 participants (371 participants in each intervention group) (Table 3).

**Table 3 T3:** Sample size estimations

**Outcome**	**Minimum relevant difference**	**Risk of type I error**	**Risk of type II error**	**Total number of participants needed**
Total sick days	5 days (SD* 21 days)	1.67%	20%	742
DLQI^†^	1.2 points (SD 4.8 points)	1.67%	20%^‡^	672
Subjective assessment of hand eczema severity	20% risk reduction from 60% event rate in the control group	1.67%	20%^§^	720

*Standard deviation of the mean.

^†^Dermatology Life Quality Index.

^‡^Will be reduced to 15.7% when 742 participants are included.

^§^Will be reduced to 18.6% when 742 participants are included.

For the DLQI, we used a standard deviation of 4.8 points [37]. In order to detect a difference between the two intervention group of 1.2 points (corresponding to 25% of the standard deviation), we will need to include 672 participants (336 participants in each intervention group). By inclusion of 742 participants, the risk of type II error will be reduced to 15.7% (power of 84.3%).

For the subjective assessment of hand eczema severity, prior data indicate that the proportion of participants with moderate to severe symptoms is 60% [38]. If the proportion of participants with moderate to severe symptoms can be reduced to 48% (relative risk reduction of 20%) in the experimental group, we need to include 720 participants (360 participants in each intervention group). By inclusion of 742 participants, the risk of type II error will be reduced to 18.6% (power of 81.4%).

In total, we will include 742 participants in the PREVEX trial, which was the maximum number of participants needed according to the three calculations.

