## Background

Occupational hand eczema is the most frequently recognised occupational disease in Denmark [1]. The incidence is approximately 0.32 per 1,000 persons in the total population [2], and the numbers are comparable in most of the industrialised world [3].

In 2011, the Danish National Board of Industrial Injuries recognised a total of 1,395 individuals with occupational skin diseases, and the large majority of these patients (> 90%) had occupational hand eczema.

Hand eczema affects mainly young people as 1/3 has onset of disease before the age of 20 years [2]. The lifetime prevalence is almost twice as high in women as it is in men [1]. This is mainly due to women’s higher exposure to wet work, occupationally as well as privately, which are well known risk factors [3]. Other aggravating factors are atopic dermatitis and contact allergy [1].

Hand eczema often takes a chronic course. A Swedish follow-up study reported active eczema 12 years after onset of disease in 72% of the sample of patients and found that 15% had been excluded from the work force [4]. In a Danish study, similar data were reported [5,6]. During a one-year period, 20% of patients with notified hand eczema had sick leave for more than five weeks due to skin disease, and 20% to 25% had loss of job (examined in the time span between notification and recognition). 57% had sick leave because of skin disease during the first year after notification. These data show that the burden of the disease is high in a personal as well as in a socio-economic context [7]. The number of persons with occupational hand eczema has remained unchanged despite public initiatives to reduce exposures to harmful allergens [8].

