### Plan for statistical analyses

#### Analysis of the three primary outcomes

##### Types of analyses

Depending on the specific type of outcome measure, one of three types of regression analyses will be applied.

• *Type 1* includes a rate (count of events over period of observation (12 months according to plan). Using the countreg procedure (SAS 9.3), the Poisson model, and the negative binomial model, the rate will be compared by testing for overdispersion and comparing the average predicted count probabilities and the observed proportions. The best model will be used to analyse data.

• *Type 2* includes a continuous outcome measure. The general linear univariate model will be used.

• *Type 3* The ordinal outcomes will be analysed using the proportional odds model where the intervention group indicator is included as a co-variate provided the P value of the score test of the proportional odds assumption is ≥ 0.05.

All of the above analyses will include the three protocol specified stratification variables (age groups, self-reported hand eczema severity, and profession) as covariates in addition to the intervention indicator and baseline value if available. If the assumptions of an analysis are seriously violated, a non-parametric test will be used.

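### The sick-leave sample size raises the expected mean from 6.74 to about 20 days but keeps the healthy-cohort SD of 21, so the stated 80% power is unsupported and probably too high

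*Protocol article*

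**What the plan says.** Total sick leave is one of three co-primary outcomes. Its sample size, 742, is the largest of the three in Table 3 (DLQI 672, severity 720) and so sets the size of the trial.

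The source of the spread is a general cohort: "In this cohort of 9,786 healthy individuals, the mean number of sick days in year 2010 was 6.74", with a 95% confidence interval of 6.32 to 7.15. The expected mean in the trial is then raised: "we estimate that the mean number of total sick days in the PREVEX trial will be higher, probably about 20 sick days per year". The next step goes back to the cohort for the SD: "From the data above, we calculated the standard deviation (SD) using this formula", which yields 21.0. Table 3 carries the same value ("5 days (SD* 21 days"), and the text concludes: "To detect a difference in total sick days of 5 days (25% risk reduction), we need 742 participants (371 participants in each intervention group"). The type I error is 1.67% and the power 80%.

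The outcome will be analysed as a rate. Under Types of analyses the candidates are named: "Using the countreg procedure (SAS 9.3), the Poisson model, and the negative binomial model", with the choice guided by a test for overdispersion.

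The Background describes the patient population: over one year, "20% of patients with notified hand eczema had sick leave for more than five weeks due to skin disease".

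**The concern.** The effect is scaled to patients and the spread is not. Five days is 25% of 20, so the difference belongs to the patient population, while the SD belongs to healthy workers with a third of that mean. In the cohort the SD is about three times the mean (21/6.74 = 3.1). Keeping 21 at a mean of 20 assumes that this ratio drops to 1.05 in patients, and the article gives no reason for it.

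Three things in the article point to a larger SD: the skewed cohort figures themselves, the plan for count models in which variance rises with the mean, and the long right tail reported for notified patients. If the SD is larger, the power for the outcome that fixes the trial size is below the published 80%. A non-significant sick-leave result would then be read against a power that the trial may not have had.

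**Working it through.** **Inputs (Sample size estimation and Table 3).** Cohort n = 9,786, mean 6.74, CI 6.32 to 7.15; expected patient mean about 20; difference 5 days; alpha 0.05/3 = 1.67%; 371 per arm. Sidedness is not stated; two-sided reproduces the stated figure.

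**Reproducing the plan.** SD = √9,786 × (7.15 − 6.32)/3.92 = 20.95, stated as 21.0. Normal approximation: n per arm = 2 × (2.394 + 0.842)² × 21²/5² ≈ 370. With the t distribution, 371 per arm gives 80.0% power, so 742 reproduces. There is no slack: by the normal formula, 80% is lost once the SD passes 5/(2.394 + 0.842) × √(371/2) = 21.05.

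**Comparison of means at other SDs.** Power = Φ[5/(SD × √(2/371)) − 2.394]; detectable difference at 80% power = (2.394 + 0.842) × SD × √(2/371).

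| SD | 5/SE | Power | Detectable difference |
|---|---|---|---|
| 21 | 3.24 | 80% | 5.0 days |
| 25 | 2.72 | 63% | 5.9 days |
| 30 | 2.27 | 45% | 7.1 days |
| 36.2 | 1.88 | 30% | 8.6 days |

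The last row assumes variance proportional to the mean: 21 × √(20/6.74) = 36.2. The 15-day arm would then have a smaller SD. With unrounded inputs the arm SDs are 36.1 and 31.2, pooled 33.8, and power is 35%.

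**Planned negative binomial test, 20 versus 15 days.** Variance = mean + k × mean², so k = (SD² − 20)/400, with SD referring to the 20-day arm. SE of the log rate ratio = √[(1/20 + 1/15 + 2k)/371]; ln(20/15) = 0.288; power = Φ(0.288/SE − z), with z = 2.394 at 1.67% and 1.960 at 5%.

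| k | SD at mean 20 | SE | Power, alpha 1.67% | Power, alpha 5% |
|---|---|---|---|---|
| 1.05 | 21 | 0.077 | 91% | 96% |
| 1.4 | 24 | 0.089 | 80% | 90% |
| 2 | 29 | 0.105 | 63% | 78% |
| 3 | 35 | 0.128 | 44% | 61% |

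The planned model therefore has room for about three extra days of SD at the strictest alpha.

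**Rough check against the Background.** Suppose 20% of patients average m days and the overall mean is 20. The variance between that 20% and the rest is 0.2(m − 20)² + 0.8[(20 − 0.2m)/0.8 − 20]² = 0.25(m − 20)², an SD of (m − 20)/2. At m = 62 this already equals 21, and at m = 80 it equals 30, before any variation within either group. The article says only that these patients exceeded five weeks, so m is an assumption.

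**The case against.** Much of the case on the other side stands.

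- **No calculation error.** The SD formula and 742 both reproduce. The fault is an unsupported input.
- **No patient SD in the article.** An SD of 21 at a mean of 20 is possible. A reader might infer that 80% power is definitely not delivered; the documents do not show that.
- **Keeping the cohort's dispersion is not credible.** From the cohort, k = (441 − 6.74)/6.74² = 9.56. At mean 20 this gives an SD of 62, with power of 10% for means and 13% for the negative binomial test. A reader might take these as the real figures. But that distribution puts 58% of patients at zero total leave and only 13% above 35 days. The Background reports 57% with skin-related leave, which caps zero total leave at 43%, and 20% beyond five weeks for skin disease alone. The scenario conflicts with the article on both counts.
- **The Background does not refute SD 21 through the share with no leave.** An SD of 21 at mean 20 implies about 5% with zero leave under the negative binomial, and it is tempting to set this against the 43% without skin-related leave. That 43% concerns eczema-related leave, whereas the outcome is total leave. It is only an upper limit, and 5% does not contradict it.
- **The planned analysis helps.** The negative binomial test has 91% power at the stated SD. Hommel's procedure is uniformly more powerful than Holm's, and a later step at 5% raises power. Covariate adjustment may also help, but to restore 80% in the comparison of means at SD 30 it would have to explain 1 − (21.05/30)² = 51% of the variance.
- **Limited reach.** Sick leave adds only 742 − 720 = 22 participants over severity.

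None of this supplies a reason for using the healthy-cohort SD at three times the mean.

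**Conclusion.** The point holds as an unsupported planning assumption. The stated 80% power for a 5-day difference in sick leave rests on an SD from a population with a third of the expected mean, and it is probably too high. Over SDs from 21 to about 36, power for a comparison of means runs from 80% down to 30%. Under the planned negative binomial test it runs from 91% at SD 21 to 44% at SD 35 at alpha 1.67%, or 61% at SD 35 if alpha is 5%.

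This rests on the usual rise of the SD of an overdispersed count with its mean, on means of 20 and 15, on complete data for 371 per arm and, for the count model, on a common dispersion in both arms. How far power falls cannot be fixed from the documents. The figures for DLQI (84.3%) and severity (81.4%) do not use this SD and are unaffected.

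**What to change.** Replace the single SD 21 row for total sick days in Table 3 with power for 742 participants, or the difference detectable with 742, over a stated range of SDs or dispersions at a mean of 20. SD 21 to about 36 would be a reasonable span. Calculate it for the planned count model, and state the assumed relation between variance and mean. The cohort's own dispersion should not be the main case.

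Before unblinding, update the table with the pooled SD, blind to arm, from the sick-leave data already collected every eight weeks. A restatement after unblinding would look driven by the result.

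The cost is a recalculation and revised wording. No extra participants and no change to the analysis are needed; the stated power for this one outcome becomes less favourable.

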#### End of follow-up, 12 months after inclusion

Participants fill in a follow-up questionnaire regarding self-reported level of eczema severity using a photographic guide [29], health-related quality of life (the Dermatology Life Quality Index) [30], level of knowledge concerning prevention of hand eczema, occupational exposure and performance management. The follow-up questionnaire will be distributed by mail to all participants and when returned, entered into SAS by scanning and where that is not possibly, manually, by external assistants. Data on absence from the work force for a period longer than 28 days will be collected from the DREAM register [31]. Further, data regarding potential effect modifiers, i.e., the participants’ use of topical corticosteroids will be collected from The Danish National Database of Reimbursed Prescriptions [32], and visits with a dermatologist will be retrieved from The National Health Insurance Service Registry [33]. Data from both national registers will be collected using the unique Danish Civil Registration Number.

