### Expected participant recruitment

A former study using a questionnaire on patients with occupational skin disease conducted in 2002 achieved a high response rate of 82% [6]. According to statistics from the National Board of Industrial Injuries, approximately 1,000 individuals reported a skin-related industrial injury in 2010 in Region Zealand and in the Capital Region of Denmark. Therefore, we conservatively assume that we will be able to complete recruitment of the 742 participants within 18 months.

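### The 742 to be randomised is the number needed with complete outcome data, so the stated powers hold only if all 742 are analysed

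*Protocol article*

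**What the plan says.** The Sample size estimation section sizes the trial separately for each co-primary outcome: "we thus used a risk type I error of 1.67% and a risk of type II error of 20% (80% power"). For sick days: "To detect a difference in total sick days of 5 days (25% risk reduction), we need 742 participants (371 participants in each intervention group"). DLQI needs 672 and severity needs 720. The rule for combining them is that "the largest of the three sample sizes is chosen to secure that the power will be at least 80" per cent.

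The largest figure then becomes the enrolment target without change: "In total, we will include 742 participants in the PREVEX trial, which was the maximum number of participants needed". The Abstract gives the same 742 as the number to be randomised. The gains in power for the other two outcomes are also expressed per participant enrolled: "By inclusion of 742 participants, the risk of type II error will be reduced to 15.7% (power of 84.3" per cent) for DLQI, and likewise 81.4% for severity. The Table 3 footnotes repeat both.

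Elsewhere the article provides for incomplete outcomes. The section on participant withdrawal covers withdrawn consent, participants who cannot be reached, and a letter to those who do not return the 12-month questionnaire. Missing values sets a rule that applies if more than 5% are missing on any primary outcome. Sensitivity analyses adds extreme-value imputations. DLQI and severity at 12 months depend on one mailing: "The follow-up questionnaire will be distributed by mail to all participants".

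**The concern.** A sample size formula returns the number of participants whose outcomes enter the analysis. Here that number is reused as the number randomised, and power is quoted as if the two were the same. This needs complete outcome data in an open-label trial whose two questionnaire outcomes come by post a year after allocation, and whose own procedures provide for some data not arriving.

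At stake is the stated type II error of each co-primary outcome. If it is too favourable, a null result will be read as stronger evidence against a relevant effect than it is. Sick days matters most, because that outcome set the 742 and has nothing in reserve. This is an explicit claim about power at a stated enrolment, not a detail left to an analysis plan that is not shown.

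**Working it through.** **Inputs, all from the Sample size estimation section and Table 3.** Sick days: "5 days (SD* 21 days"). DLQI: difference 1.2, SD 4.8. Severity: 60% versus 48%. Alpha 0.05/3 = 1.67%, target power 80%. Allocation is 1:1 (Randomisation section). The article does not say whether the tests are two-sided; two-sided tests reproduce its figures.

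**Reproducing the sample sizes.** For means, n per group = 2(z_α + z_β)²(SD/δ)², with z_α = 2.394 and z_β = 0.8416, so (z_α + z_β)² = 10.469.
- Sick days: 2 × 10.469 × (21/5)² = 369.4, so 370 per group or 740 in total. The noncentral t gives 79.9% power at 370 per group and 80.03% at 371, so 742.
- DLQI: 2 × 10.469 × (4.8/1.2)² = 335.01, so 336 per group or 672.
- Severity: two proportions, pooled variance under the null, no continuity correction: 360 per group or 720. (With a continuity correction it would be 754, so the uncorrected form was used.)

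**Reproducing the powers.** With 371 analysed per group, noncentral t for the means and the pooled formula for the proportions give 80.0%, 84.2% and 81.4%, against the stated 80%, 84.3% and 81.4%. The plan's arithmetic is sound, but only with all 742 analysed.

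**Power with loss.** The same formulas with n per group = 371 × (1 − loss). The loss is an assumption, because the article states none.

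| Assumed loss | Analysed | Sick days | DLQI | Severity |
|---|---|---|---|---|
| 0% | 742 | 80.0% | 84.2% | 81.4% |
| 5% | 705 | 77.6% | 82.1% | 79.0% |
| 10% | 668 | 75.0% | 79.7% | 76.5% |
| 15% | 631 | 72.2% | 77.0% | 73.7% |
| 20% | 594 | 69.1% | 74.0% | 70.6% |

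**Margin before 80% is lost**, from the plan's own sample sizes.
- Sick days: 742 needed of 742, so none.
- Severity: 1 − 720/742 = 3.0%, or 22 participants.
- DLQI: 1 − 672/742 = 9.4%, or 70 participants.

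**The case against.** The strongest reply is that these recomputed powers belong to simple tests the plan will not use.

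- **Sick days.** Days are collected every eight weeks and analysed as a rate over the period observed, so someone who stops partway still contributes. This stands: treating each lost participant as contributing nothing makes the sick-days column a worst case.
- **DLQI.** Baseline DLQI is collected and adjusted for. With 608 analysed (18% loss), 80% power needs 1 − r² = 608/672 = 0.905, a baseline-to-12-month correlation r of about 0.31. An r of about 0.42 (r² = 0.18) offsets the whole loss. No correlation is given in the article.
- **Severity.** The outcome is planned as ordinal, while the calculation dichotomises it. With the same odds ratio, (0.60/0.40)/(0.48/0.52) = 1.625, and 608 analysed, a Whitehead-type calculation gives 77% to 83% across four assumed five-level control distributions.
- **Multiplicity.** Hommel's procedure is at least as powerful as the Holm procedure assumed for sizing.

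All of this shows that some power may be recovered. None of it is counted in the article as an allowance for loss, and each gain depends on a figure the article does not give. Multiple imputation does not in general restore information lost with a missing outcome.

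Three stronger readings are not supported.
- A reader might take the 82% in Expected participant recruitment as the trial's retention and conclude that all three powers fall to between 70% and 75%. That figure is what an earlier questionnaire study "conducted in 2002 achieved a high response rate of 82" per cent, and it is cited only to support recruitment.
- A reader might infer that the missing-value rule and the drop-out letter predict loss above 5%. The rule is conditional and the letter carries no percentage.
- A reader might say that 80% power fails for every outcome once anyone is lost. Only sick days lacks a margin.

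**Conclusion.** The point stands as a misstatement of power. There is no arithmetic error: the stated figures reproduce, but they describe 742 participants analysed, not 742 enrolled. The rule that the largest sample size secures at least 80% power is not delivered under the plan's own calculation once there is appreciable loss, because the outcome that set the number has no slack.

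Under that calculation, at an assumed 5% loss, two of the three outcomes are below 80%. At 10% all three are, with DLQI only just under at 79.7%. At 20% the type II errors are about 31%, 26% and 29% for sick days, DLQI and severity.

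These sizes rest on the plan's SDs and effects, a two-sided alpha of 1.67%, unadjusted tests, and loss treated as complete absence of the outcome. They are the plan's own calculation carried through to a smaller number analysed, not a forecast of the power of the final models. Because the article gives no expected retention, the result is a range and not a single corrected figure.

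**What to change.** In the Sample size estimation text and the Table 3 footnotes:
- state that 80%, 84.3% and 81.4% apply to 742 participants analysed;
- add the powers over a 5% to 20% loss, labelled as an assumption, noting that the sick-days values are a worst case;
- qualify or withdraw the statement that power is at least 80% with 742 enrolled.

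If the investigators wish to rely on covariate adjustment, the ordinal severity model or Hommel's procedure to absorb loss, they should say so and give the assumption used.

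This changes wording only. It needs no extra participants, visits or data. The cost is a less favourable stated power.
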